## Abstract

**Background:**

Chemotherapy-related cognitive impairment (CRCI) and cardiac dysfunction (CRCD) are common adverse effects seen in breast cancer patients undergoing chemotherapy. Even though these effects significantly influence daily functioning and overall quality of life, effective strategies to avoid and/or mitigate these adverse effects remain elusive. Yoga as a Mind-body intervention has been used increasingly by cancer patients and has undergone empirical investigations as a potential intervention for patients with cancer. Furthermore, yoga is associated with improved cognition and cardiac functioning in healthy older adults and subjects with cognitive and cardiac impairments. Accordingly, in the current study, yoga holds promise as an intervention to prevent/manage CRCI and CRCD with improved overall QOL in women receiving chemotherapy for breast cancer.

**Methods:**

The study is a two-arm, randomized controlled trial. Women diagnosed with stage I-III breast cancer and awaiting neo-adjuvant or adjuvant chemotherapy will be recruited from a tertiary care center in Bangalore, India. Following recruitment, subjects are randomized to the intervention group (integrated yoga therapy intervention during chemotherapy) or the control group (standard care during chemotherapy). The study’s primary outcome is to measure the quality of life (cognitive domain) using European Organization for the Research and Treatment of Cancer Quality of Life Questionnaire (EORTC QLQ-C30). The other primary objectives will include cognitive functioning using neuropsychological test battery and cardiac autonomic function testing using heart rate variability. Secondary outcomes are Brain-derived neurotrophic factor (BDNF), brain function (functional MRI), Echocardiography, serum cortisol, Functional assessment of cancer therapy-cognition (FACT-Cog V3), perceived stress scale and Ryff Scales of Psychological Well-Being. Assessments take place before, during and after chemotherapy; 16-weeks post chemotherapy and 1-year post-baseline.

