#### Sample size estimation

Considering the effect size observed, in an earlier study by Vadiraja & Rao et al. (31), with improvement in cognitive function domain of EORTC Qol-C30 between yoga and control group as 0.49 with a 95% confidence interval and 80% power, we need a sample size of 67 subjects in each arm. If attrition is within 20% through the course of the intervention, 75 subjects will be recruited in each arm. Therefore 150 consenting subjects will be randomized into each group (yoga, n=75, and controls, n=75) with an allocation ratio of 1:1. The analyses would consider a two-tailed probability of p < 0.05 as significant. This ensures that a statistical type I error (probability of detecting a false positive) is less than 5%. The analyses will involve ANCOVA using the respective baseline measure as a covariate.

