### Data collection

#### Assessment of cognitive functioning

Participants complete a neuropsychological test battery at four of the five study time points [baseline (pre-intervention), end of chemotherapy (post-intervention/primary endpoint), 16 weeks post-chemotherapy (first follow-up), and one-year post-baseline (second follow-up)]. The battery covered attention/working memory, verbal and visual memory, executive functioning, planning and processing speed. These cognitive domains were chosen because previous studies have shown that they are sensitive to the deleterious effects of chemotherapy (46). The tests are performed in the following order: Colour Trials Test conditions 1&2 (attention), Digit Span Test (Memory and Recall), Stroop Test (Executive functioning), Digit-Symbol Substitution Task (processing speed), Rey auditory Verbal Learning Test (Verbal Learning and memory), Tower of London (planning and executive functioning), and Visual Reproduction task (visual learning and memory). To minimize the effects of practice, different testing forms are used at different time points. The scheme of Neuropsychological test battery planned to use in the study is depicted in **Table 2**.

**Table 2 T2:** Neuropsychological test battery.

Domain	Functions	Test	Source	Time Taken
Speed	Mental Speed	Digit Symbol Substitution	NIMHANS Neuropsychology Battery	5-7 minutes
Attention	Focussed Attention and Cognitive Flexibility	Colour Trails Test 1 & 2	NIMHANS Neuropsychology Battery	8-10 minutes
Executive Function/ Language	Phonemic Fluency	Controlled Oral Word Association Test	NIMHANS Neuropsychology Battery	5 minutes
	Semantic Fluency	Animals Names Test	NIMHANS Neuropsychology Battery	3 minutes
Executive Functions	Verbal Working Memory	Verbal N Back Test (1 back and 2 Back)	NIMHANS Neuropsychology Battery	5-7 minutes
	Response Inhibition	Stroop Test	NIMHANS Neuropsychology Battery	10-12 minutes
Visuo-Spatial	Visuo-Spatial Construction	Rey Complex Figure Test	NIMHANS Neuropsychology Battery	10-15 minutes
Learning and Memory	Visual Memory	Rey Complex Figure Test		
	Verbal Memory	Rey Auditory Verbal Learning Test	NIMHANS Neuropsychology Battery	15 minutes
Language	Speed Reading	Comprehension

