#### Heart rate variability (HRV)

The basal cardiac autonomic status will be evaluated using heart rate variability, which measures sympathetic or parasympathetic dominance. The Electrocardiogram (ECG) is recorded for 20 min, in which 5 min artefact free and resting segment will be used for analysis. Ag/AgCl solid adhesive pre-gelled electrodes (3M) will be used. The ECG will be acquired using an ambulatory ECG system (AD Instruments) at a sampling rate of 1024 Hz and will be stored for offline analysis. The data would be analysed with an advanced HRV analysis software program (LAB CHART PRO) that is inbuilt in the system.

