## Strength of the study

The trial (1) recruits an adequate sample size to detect clinically meaningful changes in cognitive and cardiac functioning, (2) includes both self-report and objective measures of cognitive and cardiac functioning, and (3) assesses outcomes at five timepoints across a 1-year period. Finally, attendance and adherence data to the yoga intervention will provide helpful information regarding women’s ability and willingness to participate in the intervention that lasts five days per week throughout chemotherapy.

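### Three outcome families have primary status, but the 5% error claim and the sample size fit only one of them, and two significance thresholds stand unreconciled

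*Protocol article*

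**What the plan says.** The abstract's methods paragraph states "The study’s primary outcome is to measure the quality of life (cognitive domain) using European Organization for the Research and Treatment of Cancer" (the QLQ-C30) and follows it with "The other primary objectives will include cognitive functioning using neuropsychological test battery and cardiac autonomic function testing using heart rate variability". Secondary outcomes come in a separate sentence, and neither the battery nor heart rate variability (HRV) is among them.

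The section on assessment of cognitive functioning labels one of the battery's visits "end of chemotherapy (post-intervention/primary endpoint". It describes the content as "The battery covered attention/working memory, verbal and visual memory, executive functioning, planning and processing speed", without a composite or a lead test. The HRV section says "The basal cardiac autonomic status will be evaluated using heart rate variability, which measures sympathetic or parasympathetic dominance", without naming an index.

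The sample size section takes "improvement in cognitive function domain of EORTC Qol-C30 between yoga and control group as 0.49 with a 95% confidence interval and 80% power" and arrives at 67 per arm. It sets a two-sided 0.05 level, names ANCOVA adjusted for baseline, and concludes: "This ensures that a statistical type I error (probability of detecting a false positive) is less than 5" per cent.

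The statistical analyses section instead describes a repeated-measures ANOVA with Bonferroni correction and a threshold of p ≤ 0.008, linked to two groups over three time points. The strengths section says that the trial "recruits an adequate sample size to detect clinically meaningful changes in cognitive and cardiac functioning".

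**The concern.** A type I error statement is only as good as the set of tests it covers. If three outcome families all count as primary and each is tested at 0.05, the error rate for the set is not below 5%. The one Bonferroni threshold in the article appears to be built from group-by-time cells, not outcomes, and it differs from the level used to size the trial.

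Two things are at stake. A favourable result on any one of the three families could be presented as success of a trial said to hold its error at 5%. And a null HRV or battery result could be read as evidence of no effect because the sample was declared adequate, although no calculation for those outcomes is given.

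**Working it through.** **Inputs.** From the sample size section: standardised effect d = 0.49, two-sided α = 0.05, power 80%, 67 per arm. From the statistical analyses section: threshold 0.008. From the abstract: three families with primary status. Assumed, because the article does not give them: the number of tests counted, the correlation between test statistics, and d = 0.49 wherever it is applied to the battery or HRV.

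**1. Reproduce the plan's figure.** n = 2(1.960 + 0.842)² / 0.49² = 65.4, so 66 per arm by the normal formula. The t-test version gives 66.35, rounded up to 67, as stated. A one-sided test would need 52. The figure is therefore right for one outcome at two-sided 0.05.

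**2. The 0.008 threshold.** 2 groups × 3 time points = 6, and 0.05/6 = 0.0083. This is an inference, as the article does not show the division. Nothing in it counts outcomes.

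**3. Number of tests.** The minimum is three, one per family. The battery text lists seven tests. Table 2 lists eight distinct tests, or nine if its incomplete last row is counted. Adding EORTC and one HRV index gives 7 + 2 = 9 to 9 + 2 = 11.

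**4. Chance of at least one false positive.** For k independent tests this is 1 − (1 − α)^k. For example, 1 − 0.95³ = 14.3% and 1 − 0.992³ = 2.4%. Correlated cases were simulated with 400,000 sets of equally correlated normal statistics.

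| Tests | Threshold | Independent | Correlation 0.5 | Correlation 0.7 |
|---|---|---|---|---|
| 3 | 0.05 | 14.3% | 12.6% | 10.9% |
| 9 | 0.05 | 37.0% | 26.9% | 20.3% |
| 11 | 0.05 | 43.1% | 30.5% | 22.2% |
| 3 | 0.008 | 2.4% | 2.2% | 1.9% |
| 9 | 0.008 | 7.0% | 5.5% | 4.3% |
| 11 | 0.008 | 8.5% | 6.5% | 4.7% |

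**5. Power under each threshold, 67 per arm.** 0.49 × √(67/2) = 2.836, and power is Φ(2.836 − z).

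- α = 0.05: Φ(2.836 − 1.960) = 81% (t-test 80%).
- α = 0.008: Φ(2.836 − 2.652) = 57% (t-test 56%). For 80% power, n = 2(2.652 + 0.842)² / 0.49² = 102 per arm (t-test 104).
- α = 0.05/3 = 0.0167, a Bonferroni split over three families with d = 0.49 assumed for each: Φ(2.836 − 2.394) = 67% (t-test 66%). For 80% power, 88 per arm (t-test 89).

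These figures describe a two-group comparison at one time point, as the plan's own calculation does. They take no credit for baseline adjustment, because no correlation with baseline is stated. Power for the interaction test itself cannot be derived from the article.

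**The case against.** The abstract uses the singular for the EORTC outcome and calls the other two objectives. The trial is sized on that same outcome, and the type I error sentence stands in that paragraph. Read for that outcome alone, it is an ordinary per-test statement. The article sets no rule that success on any one outcome suffices, which the family-wise figures presuppose. Part of this stands: a lead outcome is identifiable and its sample size is sound. But the battery and HRV are called primary and kept out of the secondary list, and nothing stated gives EORTC precedence.

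A composite, a named HRV index and a testing order may be in the full protocol or analysis plan. Their absence from an article is not the defect. The defect lies in what the article asserts: primary status for three families, an assured error rate, and adequate size.

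A reader might infer that the plan runs at a 30% to 43% error rate. That does not follow. It requires 11 separate primary tests, all at 0.05. The article does not say that each battery test is a primary test, and it sets 0.008 for the interaction. Nor does it follow that multiplicity is uncontrolled whichever threshold applies: three tests at 0.008 stay at 2.4%, and six independent ones at 4.7%. That protection is incidental, and it comes with a threshold that the sample size does not support.

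The adequacy claim is also partly supported, because the sized outcome is itself a measure of cognitive functioning. Only the cardiac part and the objective battery lack a calculation.

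**Conclusion.** The point holds in this form. The article gives three families primary status and states two thresholds that cannot both govern. At 0.05, the level behind the sample size, the 5% claim fails across the three families: about 12.6% (assumed correlation 0.5) to 14.3% (independent), and 27% to 43% if 9 to 11 tests are counted over the same correlation range. At 0.008, three tests stay at 2.4% and 11 tests reach about 6.5% to 8.5%, but power for d = 0.49 with 67 per arm is about 57%, not 80%. So no single threshold delivers both the stated power and the stated error rate for three primary families.

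The claim of adequate size is unsupported for cardiac function and for the objective battery. This does not show that the trial is too small for those outcomes, since no effect size is given for them. The 67 per arm remains correct for the EORTC outcome tested alone at 0.05. The three-family figures rest on one test per family; the larger ones are illustrations.

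**What to change.** - Declare EORTC QLQ-C30 cognitive functioning at end of chemotherapy the single primary outcome, tested at two-sided 0.05 by the ANCOVA named in the sample size section. The time point must be written down, because the primary-endpoint label now stands only in the battery section.
- State in the statistical analyses section that the 0.008 rule does not govern that test.
- Make the battery (one composite) and HRV (one named index) key secondary outcomes, tested in that order at 0.05, each only if the preceding test succeeds.
- Leave the listed secondary outcomes as secondary, without confirmatory claims.
- Limit the type I error sentence and the adequacy claim to the EORTC outcome.

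No further patients are needed on this account: α stays at 0.05 and the 67 per arm stands. The alternative of splitting α over three primary families would need 88 to 89 evaluable per arm, assuming d = 0.49 for each. The cost of the proposed change is that battery and HRV claims become conditional on the EORTC result. It also changes the status of two declared primary objectives in a registered trial, so it must be recorded in the registration.

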**Discussion:**

Yoga is a promising intervention for preventing and/or managing chemotherapy-related adverse effects (CRAE) and enhancing the quality of life among breast cancer patients. The findings from this study may also help understand the inner mechanisms involved in the protective and restorative effects of yoga on CRAE and support the use of yoga prophylactically for breast cancer patients. In addition, the results of this study could help chemotherapy-exposed individuals with other solid cancer types who have cognitive and cardiac issues.

**Ethics and Dissemination:**

The study is approved by the ethics committee of the HealthCare Global Enterprises Ltd. Hospital (EC/434/19/01) and National Institute of Mental Health and Neurosciences (NIMH/DO/ETHICS SUB-COMMITTEE (BS&NS) 9th MEETING/2018).

**Clinical Trial Registration:**

http://ctri.nic.in/Clinicaltrials/advancesearchmain.php, identifier CTRI/2020/10/028446.

## Background

Breast cancer is one of the most frequently diagnosed cancers globally, comprising 16% of all cancer types (1, 2). Evidence suggests that chemotherapy used to treat breast cancer causes inadvertent chemotherapy-associated toxicities (3–5). However, more subtle adverse effects, such as potential changes in memory or cognition, have received little attention, despite many women reporting subjective changes in memory and the ability to think clearly during and after chemotherapy. These cognitive deficits, even mild, can cause significant psychological distress and profoundly impact daily functioning and life quality (6, 7). Chemotherapy-related cognitive impairment (CRCI) typically manifests in 75% of patients during chemotherapy (acute effect) and 35% post-chemotherapy (long-term effect)- persist for months or even years after completing chemotherapy (8–10). Multiple cross-sectional and longitudinal studies have shown subjective and objective associations between chemotherapy and cognitive impairments in breast cancer patients and survivors (11–14). In addition, meta-analyses show that women who undergo chemotherapy for breast cancer perform poorly on neuropsychological tests examining attention, executive functioning, working memory, spatial ability, verbal/language ability, and information-processing speed compared to women who have not undergone chemotherapy or controls without a history of cancer (11, 15, 16). The underlying aetiology for these cognitive deficits is unknown but presumed multifactorial and caused by direct and indirect mechanisms leading to adverse structural and functional changes, such as atrophy of cerebral grey matter and white matter demyelination (17–19). In recent years, there has been emerging data on the influence of autonomic nervous system (ANS) on cognitive functioning (20). Numerous studies ascertain that cardiovascular autonomic dysfunction (CAD) attributed to the use of chemotherapeutics called Chemotherapy-related autonomic dysfunction (CRCD) leads to prolonged activation of the hypothalamic-pituitary-adrenal (HPA) axis and the elevated glucocorticoid levels (21–24). These elevated glucocorticoids cause disturbed cardiac function such as arrhythmias, hypertension, systolic dysfunction, myocardial ischemia, thromboembolism, heart failure, cardiomyopathy or other adverse events affecting patient’s quality of life and increasing the chance of cardiovascular mortality (25, 26). The primary underlying pathophysiological mechanism involved in the entire process is believed to be caused by a generalized deficit in the cholinergic function that affects both sympathetic and parasympathetic systems of the ANS (27). On that concern, global markers that help estimate autonomic dysfunction with a prospect of excellent physiological correlate are heart rate variability (HRV) and Left Ventricular Ejection Fraction (LVEF), which could be considered a promising early biomarker of cognitive and cardiac impairment in patients receiving chemotherapy for breast cancer. Since cardiotoxicity can develop during cancer treatment - or - can occur within days, months, or years after cancer treatment, assessing LVEF plays a vital role in assessing the severity of a decrease in the systolic function of the heart and thus helps direct the management of various cardiovascular diseases (28).

All these factors of CRCI, CRCD and psychological distress contribute to increased hospital visits and costs, ultimately leading to lowered quality of life. Since, few available interventions address these chemotherapy-associated adverse (29), there is a need for evidence-based therapeutic interventions to prevent cognitive decline and cardiac dysfunction experienced by breast cancer patients during chemotherapy. Practices such as yoga have shown promising results in improving cognitive (30) and cardiac functioning as studied in subjects with cancer (31). Hence this study aims to evaluate the effects of yoga intervention on CRCI, CRCD and QOL in breast cancer patients undergoing chemotherapy.

Yoga, an ancient Indian science, is widely used all over the globe as a complementary and alternative therapy which has been increasingly used in cancer patients to reduce stress, mood states, distress and improve QOL (32). Results from earlier studies on breast cancer patients have shown yoga to reduce self-reported affective states (anxiety and depression) (33, 34), chemotherapy-induced nausea and emesis (34), improvement in post-operative outcomes such as wound healing (35), reduction in pro inflammatory cytokine TNF alpha (33), improvement in natural killer cell counts (33) and reduction in symptom distress (33). Yoga has also been shown to improve various aspects of quality of life such as cognitive function, physical function and emotional function in breast cancer patients on treatment (30, 36). Besides improving quality of life, yoga also helps reduce genotoxic stress such as DNA damage (34) morning salivary cortisol levels (31) and improve the BDNF levels (37). In breast cancer survivors with advanced metastatic disease, yoga help reduce fatigue, improve sleep and reduce symptom burden (30). Yoga has been shown to enhance QOL, cortisol rhythm, and HRV in women with breast cancer undergoing radiotherapy compared to stretching alone, suggesting that yoga benefits are due to more than simple stretching, social support, or other indirect effects (38). Furthermore, yoga normalizes gastric motility and reduced cardiac autonomic stress arousal in breast cancer patients (39).

Results from these studies suggest yoga has beneficial findings concerning cognitive and cardiac function in cancer patients. Findings from all these studies suggest that inclusion of yoga during chemotherapy should not only bring alleviation from cognitive ill-effects of chemotherapy but also address issues resulting to it like distress, positive and negative psychological effect, and thereby improve quality of life. Thus, we aimed to determine the effect of integrated yoga therapy program on cognition and cardiac function assessed using EORTC QLQ-C30, Neuropsychological test battery, fMRI, blood sampling, HRV, 2D echocardiography and subjective questioners in breast cancer patients receiving chemotherapy. The results expected from the current study could be used as a preventive perspective in minimizing the risk of developing cognitive impairment by subclinical detection of cardiac autonomic dysfunction during chemotherapy and improving overall well-being.

## Methods/design

### Aims and objectives

The overall aim of the study is to examine whether Integrated Yoga Therapy Program (IYTP) can improve cognitive functioning, cardiac functioning, and quality of life in breast cancer patients receiving chemotherapy.

The objectives are as follows:

To investigate the effect of IYTP on cognitive impairment in breast cancer patients undergoing chemotherapy.To assess the role of IYTP on functional cognitive domains that affect neural circuitry changes using fMRI and effect of IYTP on treatment-related distress, perceived stress, and quality of life.To assess cardiac autonomic dysfunction using heart rate variability and associate its changes with cognitive performance.To investigate the impact of IYTP on brain-derived neurotrophic factor (BDNF) and cortisol, which in turn has its role on cognition and cardiac function.

### Study design

The study is a two-arm, parallel-group Randomised Control Trial. The design adheres to the Standard Protocol Items Recommendations for Interventional Trials (SPIRIT) (40) and the Consolidated Standards of Reporting Trials (CONSORT) (41). After completing a baseline (pre-chemotherapy) assessment, recruited women are randomly assigned to one of two groups: (I) yoga intervention, in which they receive an integrated yoga therapy program during chemotherapy (YI), or; (II) standard care control condition, in which they receive routine care during chemotherapy (SC). Additional evaluations occur mid-way through chemotherapy, post-chemotherapy, 16-weeks post-chemotherapy (first follow-up), and one-year post-baseline (second follow-up). **Figure 1**: outlines the trial design, and **Figure 2**: summarizes the enrolment schedule, intervention and assessment points.

